# 5. INTERVENTION

## 5.1. Compensatory Scanning Training

The compensatory scanning training is described in a detailed treatment protocol that will be included in the set of available training methods at Royal Dutch Visio. During the past 10 years, Visio North has built up extensive expertise of compensatory scanning training, partly based on previous PhD research in Groningen. This has resulted in a detailed training protocol. During the training, the patients’ awareness and understanding of the nature of their deficit is increased step by step and patients are taught to make eye movements towards the blind side with increasing size. After a number of sessions, these eye movements are combined with head movements and applied in mobility situations of increasing complexity. The goal is that after training, participation of the patients has increased by a decrease in mobility restrictions.

# 6. METHODS

## 6.1. Study parameters

### 6.1.1. Primary outcome measures

Scanning strategy based on eye tracking (fixation and saccade parameters) on a Dot Counting Task (similar to the Dot Counting Task as used by Zihl, 1995 [2]).

The order of research questions as listed in chapter *2 Objectives and research questions*, reflects the build-up of possible causal relations regarding the possible effect of the intervention. The eye movement parameters are on the base of this build-up. After all, in case the intervention would lead to an improvement in self-reported mobility and quality of life, but not to an improvement on the eye movement parameters, it would be hard to argue that the improvement can be ascribed to specific aspects of the training. A non-specific effect of training cannot be ruled out completely in a study like this, even more so because the control group does not receive a placebo intervention. This is one of the considerations to take eye movement parameters as the primary outcome in the power calculation. A second reason was that the dependent variables in the previous studies (all within-subject repeated-measures designs) on the effect of CST mainly used these eye movement parameters on visual search tasks and not questionnaires on mobility and quality of life [3]. Although these outcome parameters are of larger clinical importance than eye movement parameters, they could not be taken as primary outcome in the power calculation, because the expected effect size could not be predicted based on the literature.

### 6.1.2. Secondary outcome measures

*Visual functions:*

- Visual field, with Goldmann (2x monocular)
- Visual acuity, with ETDRS 2000 letter chart at 500 lux
- Contrast sensitivity, with Gecko at 500 lux

*Questionnaires (see also F1.Questionnaires)*:

- Awareness; based on theories on awareness by Crosson [7] and Critchley [8] and piloted in a group of patients with hemianopia.
- Life events; questions based on the Life Events Questionnaire (LEQ) [9].
- Motivation; questions selected from Motivation for Traumatic Brain Injury Rehabilitation Questionnaire (MOT-Q) [6].
- Expectations/Evaluation of training; questions based on interviews from previous master thesis research at UMCG Beatrixoord.
- NEI-VFQ25 (National Eye Institute - Visual Functioning Questionnaire/25 items, Dutch translation)
- VOM (Vragenlijst Onafhankelijke Mobiliteit, Dutch translation of the Independent Mobility Questionnaire)
- CVD (Cerebrale Visuele Stoornissen, Dutch translation by M. L. M. Tant, 1997)

*Neuropsychological testing:*

- Grey Scales
- NLV (Nederlandse Leestest voor Volwassenen)
- Zoo-map (BADS)
- 15-Words Test

*(Ecological) scanning and mobility tests:*

- Dot Counting Task (with eye tracking); dots are presented on a large screen and are to be counted by the patients.
- Standardized search task (with eye tracking); search task on a large screen; patients have to indicate whether or not a target is present among distractors.
- Hazard perception pictures (with eye tracking); photos of traffic situations; patients have to indicate what action they would perform in the given situations: brake, release gas pedal or do nothing.
- Hazard perception movie clips (with eye tracking); short movies of traffic situations; patients have to indicate which overt and covert hazards are present.
- Tracking Task; test in which the patient tries to keep an imaginary car on the road in the presence of cross wind using a steering wheel (road is depicted on a central monitor) while simultaneously reacting on stimuli in the left and right periphery.
- Rides in a driving simulator
- Mobility test; walking through a corridor, with and without obstacles and with and without a cognitive dual task (digit span).

*Test for cross validation:*

- Reading test

Clarification: the questionnaires are used to examine the outcome on the activity and participation level: the NEI-VFQ25 (National Eye Institute - Visual Functioning Questionnaire/25 items), the VOM (Vragenlijst Onafhankelijke Mobiliteit) and the CVS (Cerebrale Visuele Stoornissen). Change in participation is also measured with the evaluation questionnaire in the post-assessment, based on evaluation questionnaires from UMCG-Beatrixoord. Finally, also the session reports from the therapists are deployed for this aim.

*Fitness to drive as outcome parameter:*

Most patients with hemianopia are not allowed to drive a car. The Netherlands are one of the few countries worldwide where patients with hemianopia can be declared fit to drive by the CBR by succeeding a special test of practical fitness to drive. In order to apply for such a driving test, the so-called ‘Eigen Verklaringsprocedure’ (www.cbr.nl) has to be followed. Every person with hemianopia has the right to apply for this procedure.

In the existent rehabilitation program ‘AutO-Mobility’, Royal Dutch Visio guides patients with visual disorders in safe and independent participation in motorized traffic. It is a close collaboration with the CBR, a number of certified driving schools, and the departments of Ophthalmology and Neuropsychology from the UMCG. Naturally, participants in this study also have the right for independent participation in motorized traffic. They may therefore not be abstained from this information. In practice, this indeed appears to be a frequent need in this population. Because training or driving lessons related to the program AutO-Mobility might interfere with the research program here proposed, both trajectories have to be carefully aligned in an early stage. This yields possibilities for examining the effect of scanning training on regaining a drivers’ license. Part of the participants in this study perform a test of practical fitness to drive at the CBR before and after scanning training. Based on these results, Visio and the CBR will decide on including the scanning training in the Eigen Verklaringsprocedure for people with hemianopia.

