# 1. INTRODUCTION

The largest group of visual disorders after acquired brain injury are homonymous visual field defects (HVFDs). It has been estimated that 20-30% of all patients with stroke have HVFDs [1] and that 70% of these patients show a spatially disorganized visual search strategy and disturbed visual exploration of the surroundings impairing daily mobility-related activities [2]. As a consequence, they often fail to notice relevant objects or avoid obstacles and they are often unable or afraid to walk or cycle independently. This has far-reaching, disabling repercussions on their domestic and vocational lives and participation in society. However, when patients become more aware of their deficits and learn to apply a new scanning strategy in order to compensate for the visual field defect, daily life mobility may improve substantially [3,4]. In a recently published systematic review [3], it was concluded that compensatory scanning training is the most promising approach when it comes to the level of participation in society. This training teaches patients to apply large eye and head movements towards the blind hemifield. The patient learns to enlarge the functional field of view and to compensate for the loss of visual information that would occur if no eye movements were made.

First evidence for the effects of compensatory scanning training has been found, but the training protocols that were examined differed from each other and so far, few attention has been paid to the effects on mobility. Furthermore, only studies using within-patient repeated measures designs have been performed. The randomised controlled trial (RCT) as proposed in this study protocol provides a solution for these problems.

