When the waiting list is longer than 10 weeks, the patient will be allocated to either the training group or the control group based on the random allocation described above. When the waiting list is shorter, which is not expected, the patient will be allocated to the training group in case the patient belongs to this group based on the random allocation. In case the patient would belong to the control group based on the random allocation, the patient is excluded from the study, but the patient can still start scanning training within 10 weeks. Patients from both the training group and the control group will visit the University Medical Center Groningen for a pre-assessment (the week before onset of training at Royal Dutch Visio) and a post-assessment (after 10 weeks of training). The control group will participate in a third assessment, 10 weeks before the pre-assessment. (the so-called -10 assessment). By looking at the results from the pre-assessment and post-assessments of the training group and the results from the -10 assessment and pre-assessment of the control group, the effect of 10 weeks of training is compared to the effect of 10 weeks on the waiting list. In addition, the effect of treatment on the individual level can be examined by comparing the results from the post-assessment to the results from the -10 assessment and pre-assessment in the control group (within-patient repeated measures design). Including the post-assessment in the control group also increases power of the study.

The effect measurements will be performed by (student) neuropsychologists under supervision of [name]. They are not informed about the allocation to the training group or the control group and therefore they do not know whether the patient already received training or not.

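### The driving test at the CBR is scheduled only before and after training, so it gives no waiting-list change, yet a Visio/CBR decision is to be based on the results

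*Protocol*

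**What the plan says.** The text is in Protocol Section 6.1.2, under the sub-heading on fitness to drive as an outcome parameter. It does four things.

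- It states an aim: "This yields possibilities for examining the effect of scanning training on regaining a drivers’ license".
- It sets the test times and the group tested: "Part of the participants in this study perform a test of practical fitness to drive at the CBR before and after scanning training".
- It attaches a consequence: "Based on these results, Visio and the CBR will decide on including the scanning training in the Eigen Verklaringsprocedure for people with hemianopia".
- It names a co-intervention and a response to it: "Because training or driving lessons related to the program AutO-Mobility might interfere with the research program here proposed, both trajectories have to be carefully aligned", at an early stage. How the alignment is to work is not described.

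The trial's control is defined in Sections 3 and 6.2. For the assessments at the University Medical Center Groningen, "the effect of 10 weeks of training is compared to the effect of 10 weeks on the waiting list". This is possible because of an extra visit: "The control group will participate in a third assessment, 10 weeks before the pre-assessment". The CBR test is not mentioned in connection with that visit.

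Section 1 gives the motive for the trial, namely that so far "only studies using within-patient repeated measures designs have been performed". Sections 1 and 3 rank such designs below a randomised trial.

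**The concern.** The aim is causal and a decision follows from it, but both stated tests lie on either side of the training. A patient who passes the second test after failing the first may have gained from scanning training, from having sat the test before, or from driving lessons in between. Without a change measured over an untrained period, the data cannot tell these apart.

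At stake is what may be concluded from this one outcome. It is the only outcome for which the protocol names a decision that will follow, and that decision concerns a formal procedure for people with hemianopia. The training could be adopted there on a gain that it did not cause.

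**Working it through.** **The plan's own figures.** There is none for fitness to drive. The sample size in Section 4.4 concerns eye movements: 2 × (1.645 + 0.842)² / 0.65² = 29.3, rounded up to 30 per group. It reproduces, but it has no bearing on the CBR test.

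**Test times side by side** (Sections 3, 6.1.2 and 6.2)

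| Measure and arm | 10 weeks before pre-assessment | Before training | After training |
|---|---|---|---|
| Groningen assessments, training arm | – | yes | yes |
| Groningen assessments, control arm | yes | yes | yes |
| CBR test, training arm (subset) | – | yes | yes |
| CBR test, control arm (subset) | not stated | yes | yes |

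**What each contrast contains.** For the Groningen assessments the control is a difference of two changes:

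(post − pre, training arm) − (pre − minus-10, control arm)

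- The first change holds the training effect plus repeat testing, time and other help received.
- The second holds repeat testing, time and other help, without training. Subtraction leaves the training effect if the rest is alike in both arms.
- For the CBR test the second term does not exist, because the control arm has no stated test at minus 10 weeks.
- The pre-to-post change in controls does not replace it, since controls are trained in that interval too.
- One could compare the arms once, at the time point that Section 8.2 calls T2. Trained patients would then be at their second sitting and controls at their first, so repeat testing would still be mixed with training. The protocol does not plan this for the driving test.

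**Can the bias be sized?** No. The protocol gives no number tested, no pass rates and no expected gain without training. The following is an assumption-based illustration only. Suppose scanning training has no effect, 5% of those tested go from pass to fail, and a share *c* go from fail to pass for other reasons. Apply an exact one-sided McNemar test at 0.05: among *k* patients whose result changes, *x* of them upward, declare a gain if P(X ≥ x) ≤ 0.05 under a binomial(*k*, 0.5). The probability of declaring a gain is then:

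| Assumed *c* | 20 tested | 30 tested |
|---|---|---|
| 10% | 0.02 | 0.05 |
| 20% | 0.18 | 0.34 |
| 30% | 0.45 | 0.69 |

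The range runs from no inflation to severe inflation. It depends on *c*, which the stated schedule cannot measure. The protocol does not say that this test will be used.

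**The case against.** Several counter-arguments carry weight.

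- **Role in the trial.** Fitness to drive is not among the eight research questions in Section 2, is not in the sample size, and is not named in the analyses of Section 8.3. Section 6.1.2 speaks of possibilities for examining an effect, which is cautious wording. This stands, and it limits the point to a side outcome. It does not answer the sentence that bases a decision on the results.
- **Other driving-related data are controlled.** Hazard perception, the tracking task and the simulator rides belong to the Groningen measurements and follow the waiting-list comparison. This stands too, so it would be wrong to infer that the trial as a whole falls back on the design it set out to replace. These measures are not the CBR test on which the decision rests.
- **Spontaneous recovery is limited.** Section 4.2 requires at least six months since onset and a stable neurological condition. That weakens one rival explanation but leaves repeat testing and lessons.
- **A CBR test at minus 10 weeks is not ruled out.** True, its absence is inferred. But the only times given are before and after training. An analysis plan cannot supply a test that was never scheduled.

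A reader might also infer more than the text supports.

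- *Results could only move upward because only initial failures count.* The protocol does not restrict testing or analysis to patients who fail first, and someone who passes may later fail.
- *Those tested are those who want to drive.* No selection rule is given.
- *A handful of conversions would already be significant.* Five failures turned into passes with no reversal give 0.5⁵ = 0.031, and six give 0.5⁶ = 0.016. One reversal changes this: 5 against 1 gives 7/64 = 0.109, and 6 against 1 gives 8/128 = 0.063. These values rest on assumed counts and a test the protocol does not plan.

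**Conclusion.** The point holds in a limited form. On the stated schedule no 10-week waiting-list change in the CBR test can be formed. A before-after gain therefore cannot be attributed to scanning training rather than to repeat testing or to AutO-Mobility training or lessons. The protocol names the lessons as possible interference and asks for alignment, but gives no rule for controlling or recording them.

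The size of any bias is unknown and cannot be derived from the document. The conclusion rests on one reading: that the test times in Section 6.1.2 are complete. It concerns a side outcome, and the primary comparison on the Dot Counting Task is unaffected. It would go too far to say that the results are worthless or that lessons will in fact fall between the tests. What is unsupported is basing the decision on these results as evidence of a training effect.

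**What to change.** In Section 6.1.2:

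1. State that the before-after CBR results are descriptive and uncontrolled, and do not by themselves establish an effect of scanning training.
2. Remove the sentence that bases the Visio/CBR decision on these results, or soften it so that they are one descriptive input among others.
3. Record any AutO-Mobility training or driving lessons taken between the two tests, and report them by arm.

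The first two changes are wording only, and the third needs a short record per test-taker. The downside is that the driving result becomes descriptive.

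The sponsor may weigh one further option: placing the two CBR tests at T1 and T2 in both arms (pre and post in the training arm, minus 10 weeks and pre in the control arm). That would give a randomised comparison with the same number of tests per patient. Controls would then have no post-training CBR test within the study. That is a real loss, so this is an option and not the recommended change.

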### 6.1.3. Other measures

The following biographical and medical variables with possible influence on the performance on the tests for social and general cognition will be included:

-Sex, age, comorbidity

-Time between acquired brain damage and first effect measurement

-Size (mm) and location of lesion based on brain imaging (CT, MRI)

These data will be derived from the medical records of the patients. For this aim, written consent will be requested from the patients.

## 6.2. Selection

The effects of scanning training will be examined by comparing a group of patients receiving treatment with a group of patients on the waiting list for the treatment. During this period of ‘waiting’, the latter group functions as a control group for the patients in the training stage.

Allocation is based on the method of minimization, under the condition that allocation of the patient minimizes the difference between both groups with regard to age, sex, side of field defect, size of field defect, time since lesion and training region.

Both groups need to be sufficiently equal regarding important prognostic variables. Differences between the groups on dependent variables should be able to be described to the intervention and not to the group characteristics. Theoretically, the allocated intervention should be the only difference between the groups. Therefore, it is highly important that potentially prognostic factors such as sex, age, lesion location and time since onset do not interfere with the interpretation of the group differences. Selection bias - an unequal distribution of these prognostic factors over the groups - forms the greatest threat to internal validity. Several different randomization techniques exist, which all serve a twofold purpose: every patient should have an equal a priori chance to receive either intervention and selection bias should be ruled out. Adaptive randomization, also called minimization, is a dynamic procedure, in which chances for allocation to one of the groups are influenced by the characteristics of the patients already allocated. The procedure is based on the idea that with every allocation, the differences between the groups are minimized [10]. The Consolidated Standards of Reporting Trials (CONSORT) state that “trials that use minimisation are considered methodologically equivalent to randomised trials, even when a random element is not incorporated” [11,12]. For the sample size of our study (n = 60), it is demonstrated that adaptive randomization is not only equivalent, but even superior to unconditional randomization [13].

The moment patients are definitely included for the study, the scanning training and all effect measurements are planned based on the waiting list at Royal Dutch Visio. Allocation to one of the two groups will not affect the moment at which the training starts. At Royal Dutch Visio, a waiting list of several months preceding treatment is not unusual.

When the waiting list is longer than 10 weeks, the patient will be allocated to either the training group or the control group based on the random allocation described above. When the waiting list is shorter, which is not expected, the patient will be allocated to the training group in case the patient belongs to this group based on the random allocation. In case the patient would belong to the control group based on the random allocation, the patient is excluded from the study, but the patient can still start scanning training within 10 weeks. Patients from both the training group and the control group will visit the University Medical Center Groningen for a pre-assessment (the week before onset of training at Royal Dutch Visio) and a post-assessment (after 10 weeks of training). The control group will participate in a third assessment, 10 weeks before the pre-assessment. (the so-called -10 assessment). By looking at the results from the pre-assessment and post-assessments of the training group and the results from the -10 assessment and pre-assessment of the control group, the effect of 10 weeks of training is compared to the effect of 10 weeks on the waiting list. In addition, the effect of treatment on the individual level can be examined by comparing the results from the post-assessment to the results from the -10 assessment and pre-assessment in the control group (within-patient repeated measures design). Including the post-assessment in the control group also increases power of the study.

The effect measurements will be performed by (student) neuropsychologists under supervision of [name]. They are not informed about the allocation to the training group or the control group and therefore they do not know whether the patient already received training or not.

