First of all, a detailed training protocol will be used, that will be included in the set of available training methods at Royal Dutch Visio. During the past 10 years, Visio North has built up extensive expertise of compensatory scanning training, partly based on previous PhD research in Groningen [4]. Until now, the only department of Visio experienced with this training method was located in Haren. No standardized protocol was available for this method, causing large variety in use of the method among therapists and patients. In order to recruit enough participants for the effect study, the training will be implemented throughout The Netherlands. A protocol for the training has been written by Royal Dutch Visio Haren in order guarantee unequivocality (protocol can be requested from principal investigator [name]). During the training, the patients’ awareness and understanding of the nature of their deficit is increased step by step and patients are taught to make eye movements towards the blind side with increasing size. After a number of sessions, these eye movements are combined with head movements and applied in mobility situations of increasing complexity. The goal is that after training, participation of the patients has increased by a decrease in mobility restrictions.

Second, multiple rehabilitation centers will participate in the RCT, making that the effects of training cannot be exclusively related to the expertise available within a certain region.

Third, the RCT as here proposed intends to demonstrate the effects of scanning training on several functional levels (cognitive and physiological) and multiple levels of participation and mobility.

Fourth, the effects of treatment will be examined by comparing a group of patients receiving treatment with a group of patients on the waiting list for the treatment. During this period of ‘waiting’, the latter group functions as a control group for the patients in the training stage. Allocation to one of the two groups will not affect the moment at which the training starts. In the medical-scientific literature, this method (RCT) is much more highly appreciated (class A studies) than within-patient repeated measures designs (class B or C studies).

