## 8.2. Univariate analysis

*Primaire onderzoeksparameter*

The effect of training on the fixation and saccade parameters on the Dot Counting Task are analyzed in two ways:

1. A between-group analysis by comparing data from T2 of the training group with data from T2 of the control group, possibly corrected for data from T1.
2. A within-group analysis by comparing change between T1 and T2 with change between T2 and T3 in the control group using repeated measures analysis.

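### The compared visits are about 10 weeks apart in time since allocation, so section 8.2 should make the T1 correction mandatory rather than optional

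*Protocol*

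**What the plan says.** Sections 1, 3 and 6.2 of the protocol all state that the arm does not determine when training begins. In section 6.2: "Allocation to one of the two groups will not affect the moment at which the training starts". The same section adds that "the scanning training and all effect measurements are planned based on the waiting list at Royal Dutch Visio".

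Both arms have a pre-assessment in the week before training and a post-assessment after 10 weeks of it. In addition, "The control group will participate in a third assessment, 10 weeks before the pre-assessment". Section 6.2 sets the condition for allocation to either arm: "When the waiting list is longer than 10 weeks, the patient will be allocated to either the training group or the control group".

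Two descriptions of the main comparison follow.

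- Sections 3 and 6.2 set pre-to-post in the training arm beside -10-to-pre in the control arm, so that 10 weeks of training is weighed against 10 weeks of waiting.
- Section 8.2, for the primary outcome, specifies "comparing data from T2 of the training group with data from T2 of the control group" and mentions correction for T1 only as a possibility.

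The protocol does not define T1, T2 and T3. The within-control analysis in section 8.2 uses three control-arm time points. The mapping that fits is control T1 = -10 assessment, T2 = pre-assessment, T3 = post-assessment, and training T1 = pre-assessment, T2 = post-assessment. That mapping is inferred.

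**The concern.** Training start is common to both arms, so what allocation changes is the window used for measurement. The visits that section 8.2 pairs are therefore not at the same time since allocation, or since onset. Section 6.2 says that, in theory, only the intervention should differ between the groups, and it names time since onset among the factors that must not interfere. Minimisation on time since lesion balances that factor at allocation. It cannot remove an offset that the visit schedule creates afterwards and that applies to every patient.

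Two things are at stake. Any untrained drift over 10 weeks would be credited to training in the uncorrected contrast. Also, an analyst may choose between a corrected and an uncorrected primary contrast that have different exposure to this drift.

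**Working it through.** **Plan's own figure.** Section 4.4 gives effect size 0.65, one-sided alpha 0.05, power 0.80 and two independent groups. n = 2(1.645 + 0.842)²/0.65² = 29.3, rounded up to 30 per arm. This agrees with the protocol (power at 30 per arm: 0.809). The standard error of an uncorrected difference, in SD units, is then √(2/30) = 0.258.

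**Timeline.** Let training start W weeks after allocation, with W above 10 (section 6.2).

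| Visit | Training arm | Control arm | Lag of training arm |
|---|---|---|---|
| T1 | W-1 to W | W-11 to W-10 | 10 weeks |
| T2 | W+10 | W-1 to W | 10 to 11 weeks |
| T3 | none | W+10 | – |

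The lag is the same for every W. The control visit that coincides in time with the training arm's T2 is control T3, which follows the controls' own training.

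**Bias.** Let d be untrained drift per 10 weeks, m the untrained mean 10 weeks before the pre-assessment, and b the slope of T2 on T1. Treat the T2 lag as 10 weeks.

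- Training arm: T1 = m + d, T2 = m + 2d + effect.
- Control arm: T1 = m, T2 = m + d.
- Uncorrected T2 difference: effect + d.
- T2 adjusted for T1: effect + d - b·d = effect + (1-b)d.
- Difference in change: (d + effect) - d = effect, if drift is steady.

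If the pre-assessment falls a full week before training, the training window is 11 weeks against 10, and the difference in change keeps 0.1d (0.02 SD at d = 0.2).

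**Size.** The documents give no d, b or T1–T2 correlation r. I assume d = 0 to 0.3 SD, r = 0.5 or 0.7, and equal variances, so b = r. The false-positive rate with no true effect is 1 - Φ(1.645 - bias/SE), with SE = 0.258 uncorrected and √((2/30)(1-r²)) adjusted (0.224 at r = 0.5, 0.184 at r = 0.7).

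| d (SD) | Bias, uncorrected | Bias, adjusted (r = 0.5 / 0.7) | False positives, uncorrected | False positives, adjusted (r = 0.5 / 0.7) |
|---|---|---|---|---|
| 0 | 0 | 0 / 0 | 5.0% | 5.0% / 5.0% |
| 0.05 | 0.05 | 0.025 / 0.015 | 7.3% | 6.3% / 5.9% |
| 0.10 | 0.10 | 0.05 / 0.03 | 10.4% | 7.8% / 6.9% |
| 0.20 | 0.20 | 0.10 / 0.06 | 19.2% | 11.6% / 9.4% |
| 0.30 | 0.30 | 0.15 / 0.09 | 31.5% | 16.5% / 12.4% |

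A bias of 0.10 SD is 0.10/0.65 = 15% of the planning effect.

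**Adjusted or change score.** The variance ratio of change score to covariate adjustment is 2(1-r)/(1-r²) = 2/(1+r): 1.33 at r = 0.5 and 1.18 at r = 0.7. Mean squared error is variance plus squared bias:

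| r | d | Change score | T1-adjusted |
|---|---|---|---|
| 0.5 | 0.1 | 0.067 | 0.050 + 0.0025 = 0.0525 |
| 0.5 | 0.2 | 0.067 | 0.050 + 0.010 = 0.060 |
| 0.7 | 0.1 | 0.040 | 0.034 + 0.0009 = 0.035 |
| 0.7 | 0.2 | 0.040 | 0.034 + 0.0036 = 0.038 |

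Covariate adjustment has the smaller error in all four cases.

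**Testing for drift.** The training arm's pre-assessment and the control arm's -10 assessment are both first, untrained tests, 10 weeks apart. With SE 0.258, a two-sided 0.05 test of their difference has power of about 7% at d = 0.1 and 12% at d = 0.2.

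**The case against.** The fair case against is substantial.

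- **Much is already in the plan.** Sections 3 and 6.2 describe the within-window comparison, section 8.2 foresees correction for T1, and the choice of adjustment is often left to a statistical analysis plan, which is not shown. This stands in part. What remains is that section 8.2 names the T2 contrast as the primary between-group analysis with correction optional, and does not match sections 3 and 6.2.
- **Drift may be absent.** Section 4.2 requires at least six months since onset, a stable neurological condition, and an ophthalmological condition stable for six months. Both arms have had two assessments by T2, so practice exposure is balanced. This stands, and it limits the importance of the point.
- **The timing is deliberate and disclosed.** No patient's training is moved for the study. This stands. The offset is a property of the chosen design, not a mistake in it.

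A reader might also infer three stronger things that the documents do not support.

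- That the T2 contrast contains 10 extra weeks of waiting and usual care. By T2 both arms have waited about W weeks. The training arm's further 10 weeks are the training itself, so the offset is elapsed time. Care during the wait is not described, and section 6.1.2 says the AutO-Mobility programme must be aligned with the study because it might interfere.
- That the Introduction is false in saying "the latter group functions as a control group for the patients in the training stage". The sentence concerns groups. If patients enter over time, some controls may be waiting while some training-arm patients train.
- That the change score should replace covariate adjustment, or that a drift check should decide between them. The first is a trade-off with larger mean squared error in the cases above. The second would let a test with about 7% to 12% power choose the estimate.

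**Conclusion.** The offset is real and follows from the visit definitions, given the inferred reading of T1, T2 and T3: 10 weeks at T1 and 10 to 11 weeks at T2, for any waiting time. Section 8.2 leaves open the one contrast that carries the whole of any drift, and does not agree with the comparison in sections 3 and 6.2.

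The resulting bias is not established. It is d uncorrected, (1-b)d when adjusted for T1, and zero for the difference in change under steady drift. All numerical sizes rest on assumed values of d and r, and the bias is zero if these stable patients do not drift. This is a minor point of wording and prespecification, not evidence that the trial's result would be wrong.

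**What to change.** In section 8.2:

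1. State which assessment T1, T2 and T3 denote in each arm.
2. Remove the uncorrected T2 comparison and the qualifier *possibly*. Prespecify one primary between-group analysis: T2 adjusted for T1 as a covariate. It uses both visits of each arm's window and so fits sections 3 and 6.2.
3. Give the difference in change over each arm's own window as a sensitivity analysis, because it removes steady drift.
4. Report the training arm's pre-assessment beside the control arm's -10 assessment descriptively, and not as a rule for choosing the estimate.
5. State as a limitation that the two windows are offset by about 10 weeks from allocation.

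The cost is a few sentences and one table from data already collected, with no new visits or patients. Sample size stays at 30 per arm. The sensitivity analysis is less precise than the primary, with variance about 33% higher at r = 0.5 and 18% higher at r = 0.7. The primary keeps a residual (1-b)d if drift exists.
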